### Data collection and sampling

#### Clinical assessments

After documentation of eligibility and consent in the web-based randomisations system, subsequent data collection is in Research Electronic Data Capture (REDCap) by the recruiting site staff and parents/guardians complete an App provided by Your Research B.V. (Huizen, Netherlands) to record respiratory symptoms, non-respiratory symptoms and adherence to the IMP. A WheezeScan device is provided to all parent(s)/guardian(s) to detect and differentiate wheezing from other breath sounds. If respiratory symptoms are reported on the App, the recruiting site staff will be able to access the data including reporting of respiratory symptoms, as they will have access to the App dashboard to review data entries of all participants recruited from their site. They will then verify if an LRTI has occurred.

Initial data collection in REDCap focuses on maternal history, information about the family, antenatal information, details around the infant’s birth and neonatal admission. Monthly follow-up phone calls are being carried out by the site staff at 1, 2, 4, 5, 7, 8, 10 and 11 months of age focusing on adherence, concomitant medications and ensuring the parents have adequate BALLOON IMP and swabs for the next month and all LRTIs have been verified. Face-to-face visits either at the infant’s home or in hospital take place at 3, 6, 9 and 12 months of age. The face-to-face visits focus on IMP adherence, receipt of concomitant medications, supply of new IMP sprays and weighing the returned sprays (to further aid adherence), ensuring all LRTIs have been verified, and completing ongoing medical history including any potential adverse events.

Infants remain in follow-up for safety until 13 months’ corrected age.

### Data collection

All data will be recorded on the trial electronic Case Report Form in the CHaRT or REDCap systems. Data are regularly monitored and queries are raised as necessary with sites.

### Sampling

#### Viral swabs

If the infant has any respiratory symptoms, the App alerts the parents to obtain a viral swab with details of how to obtain one shown before discharge by the recruiting site staff. The App also alerts the recruiting site research nurse when a sample is obtained/required. Recruiting sites are provided with the required materials for sample collection, labelling and transport, which they give to the parents at each study visit. The parents will post the viral swabs directly to the Wales Specialist Virology Centre at Public Health Wales in Cardiff, for batch analysis for a broad range of common seasonal viruses. An educational video showing the parents how to obtain a viral swab is shown on the BALLOON public website.

### Analysis

#### Sample size

The primary analysis involves comparing health professional diagnosed LRTIs between enrolment and 1-year corrected age between the two trial arms. Based on rates of LRTIs from previous cohorts of preterm-born infants of 46%^3 4^ and the AZTEC follow-up data showing admission rates of 55% (of 385 survivors with available data) by 1 year of corrected age (unpublished data), we estimated that 55% of participants in the placebo arm would experience a health professional diagnosed LRTI.

Our target effect size is a 15% absolute reduction (ie, reduction to 40% in the intervention arm, translating to a relative difference of 27%). This is a realistic target and of clinical importance to clinicians, health providers and parents. We assume a loss to follow-up rate of 15%, as data will be obtained from healthcare professionals and followed up by research nurses and hence completion should be high.

In order to maximise trial efficiency and allow for stopping for lack of benefit, we have included an interim analysis (stage 1) as part of this trial with an intermediate outcome of health professional diagnosed LRTIs within 6 months post-randomisation. We assume a positive predictive value between intermediate and definitive primary outcome of 1 by design (given that the intermediate outcome is the definitive outcome measured at an earlier timepoint, and outcomes are cumulative) and that the majority (37%/55%) of LRTI diagnoses occur during the first 6 months post-randomisation.

To maintain overall power of 90% and a pairwise one-sided alpha of 0.025, we require 346 recruited participants, of whom 182 will have analysable intermediate outcome data, to conduct an interim analysis with stopping for lack of benefit. Our stage 1 one-sided alpha is 0.43 and power is 97%. The unblinded interim data will be assessed independently by the Independent Data Monitoring Committee (IDMC) and recommendations made to continue the trial or not.

Should we progress from the interim analyses to stage 2, we would require 542 total recruited participants of whom 460 have analysable definitive outcome data. The stage 2 one-sided alpha is 0.025 and power is 92%.

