### Interim analysis

At the interim analysis stage, we will compare the proportion of infants experiencing at least one health professional diagnosed LRTI within 6 months between trial arms by fitting a two-level Poisson (or negative binomial/logistic) regression model, with multiple infants nested within mothers and robust standard errors. Models will also adjust for gestational age and anti-RSV prophylaxis (as per randomisation factors). Results will be reported to our IDMC as adjusted risk differences (using the margins command in Stata), 95% CIs and p values. As per our design parameters, should our one-sided p value be >0.43, this would provide statistical indication of a lack of benefit of our intervention. Additional data (eg, other outcomes, including safety data) may be considered by our IDMC when deciding whether to progress or stop at this stage.

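### The stated stage 1 (97%), stage 2 (92%) and overall (90%) power do not follow from 182 and 460 analysable infants; overall power is about 83% to 89%, depending on an unstated 6-month effect

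*Protocol article*

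**What the plan says.** All the design figures are in the protocol article under Sample size.

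- **Overall target:** "To maintain overall power of 90% and a pairwise one-sided alpha of 0.025".
- **Definitive outcome at 1 year corrected age:** "we estimated that 55% of participants in the placebo arm would experience a health professional diagnosed LRTI". The target is a fall to 40%, given as 15 points absolute and 27% relative.
- **Intermediate outcome at 6 months:** the placebo figure comes from the assumption that "the majority (37%/55%) of LRTI diagnoses occur during the first 6 months post-randomisation". The link to the final outcome is also given: "We assume a positive predictive value between intermediate and definitive primary outcome of 1 by design". No 6-month rate or target difference is given for the Bactek arm.
- **Stage 1:** "we require 346 recruited participants, of whom 182 will have analysable intermediate outcome data", and "Our stage 1 one-sided alpha is 0.43 and power is 97" per cent.
- **Stage 2:** 542 recruited, 460 analysable, one-sided alpha 0.025, power 92%.

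The Interim analysis section turns the stage 1 alpha into the futility rule: "should our one-sided p value be >0.43, this would provide statistical indication of a lack of benefit of our intervention". It adds that the IDMC may consider other data as well.

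**The concern.** At stage 1, power is the chance that an effective product passes the futility look, so 97% means a 3% risk of a false flag for lack of benefit. That figure depends on the difference expected at 6 months, which the article leaves out. The natural value to infer, from the article's own 37/55 share, is about 10 points rather than 15. A 10-point difference with 91 infants per arm does not give 97%.

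A trial with a futility look succeeds only if it passes both stages, so a higher false-stop risk lowers overall power directly. Overall power also cannot exceed stage 2 power, and the stated stage 2 power is itself a little too high for 460 infants. The IDMC would then apply the p>0.43 rule with too favourable an idea of its error rate, and the claim of 90% power would not be met.

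**Working it through.** **Inputs from the article.** Placebo 55% and Bactek 40% at 1 year; placebo 37% at 6 months; 182 analysable at the interim and 460 at the end, 1:1, so 91 and 230 per arm; one-sided alpha 0.43 and 0.025; positive predictive value 1; 15% loss; 24 months of recruitment. **Assumed:** the 6-month Bactek rate, varied from 27% to 22%.

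**1. What reproduces.**
- 460/0.85 = 541.2, hence 542.
- Reading 182 as a total: 182/0.85 = 214, plus 6 months at 542/24 = 22.6 per month, is about 350, close to 346.
- Stage powers of 97% and 92%, with the correlation of about 0.45 derived in step 4, combine to 90.0%. The three stated powers are therefore consistent with each other.

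**2. Stage 2 power (no 6-month assumption needed).**
Power = Φ(d/√[(p₁q₁+p₂q₂)/n] − z), where q = 1 − p.
- 0.15/√[(0.2475+0.2400)/230] = 3.258.
- Φ(3.258 − 1.960) = 90.3%; with pooled variance, 89.9%.
- 92% would need 246 to 249 per arm, or 492 to 498 analysable.

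**3. Stage 1 power, 91 per arm, z(0.57) = 0.176.**
The 37/55 share applied to the Bactek arm gives 40 × 37/55 = 26.9%. The 27% relative reduction is the same thing: 37 × 40/55 = 26.9%.
- 37% v 27%: 0.10/√[(0.2331+0.1971)/91] = 1.454; Φ(1.454 − 0.176) = 89.9%. At 26.9% it is 90.2%.
- The per-arm number for 97% at 37% v 27% is (0.176+1.881)² × 0.4302/0.10² = 182.06.

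**4. Overall power.** This is the bivariate normal probability of passing both stages. With predictive value 1, the covariance per infant in each arm is p(6 months) × [1 − p(1 year)]. At 37% v 27% the correlation is (0.37×0.45 + 0.27×0.60)/√(0.4302×0.4875) × √(91/230) = 0.451.

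| Bactek at 6 months | Points of benefit by then | Stage 1 power | Overall power, 460 at the end |
|---|---|---|---|
| 27% | 10 | 89.9% | 83.1% |
| 25% | 12 | 94.4% | 86.5% |
| 24% | 13 | 96.0% | 87.6% |
| 23.2% | 13.8 | 97.0% | 88.4% |
| 22% | 15 | 98.1% | 89.1% |

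Pooled variance gives 82.8% and 88.7% overall in the first and last rows. Simulation (400,000 trials, interim cases nested in final cases) gives 82.0% and 88.5%.

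**5. Futility threshold.** At 37% v 27% with 91 per arm, 97% at stage 1 would need a threshold of about 0.66, with overall power about 88%. Under no effect, the chance of a futility flag is 1 − 0.43 = 57% now, and 1 − 0.66 = 34% then.

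None of these figures allows for clustering of multiple births, which are allocated to the same arm.

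**The case against.** The strongest reply is that the 10-point effect at 6 months is not the article's. The target is stated as an absolute reduction, with the relative figure only as its translation, and the interim result is to be reported as a risk difference. Put 15 points at 6 months (37% v 22%) and 182 in total gives 98.1% at stage 1, or 97.2% with a continuity correction, with overall power about 89%. This stands, so a reader who concludes that stage 1 power simply is 90% goes further than the text allows. It is one end of a range. The reply does need all of the benefit to appear in the first 6 months, with both arms then adding the same 18 points. It also does not explain 182, since 97% at 37% v 22% needs only about 76 per arm. Nor does it restore 90% overall.

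A reader might also infer from the 182.06 above that the article printed a per-arm number as a total. That is possible but not proven. The wording makes 182 part of 346 recruited, 364 would exceed 346, and the accrual arithmetic fits a total. Another route lands nearby: 55% v 40% at alpha 0.43 and 97% power needs 91.7 per arm, about 184 in total, although those are 1-year rates.

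Finally, the rule is not binding, so the 10% false-stop risk and the 83% assume that it is followed. The full protocol or the analysis plan may state the 6-month rate. That would settle which row of the table applies, but would not change the stage 2 result.

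**Conclusion.** The concern holds as a mismatch between stated powers and stated numbers. Its size depends on the 6-month Bactek rate.

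- **Stage 2:** about 90%, against 92% stated. This rests only on figures in the article.
- **Stage 1:** about 90% if the 37/55 share applies to both arms, against 97% stated, so a false-stop risk of about 10% rather than 3% when the p>0.43 rule is followed. It is 97% or more only if about 14 or more of the 15 points have appeared by 6 months.
- **Overall:** about 83% under the proportional effect and at most about 89% if the full effect is present by 6 months, against 90% stated. No reading tested reaches 90% with 460 analysable. Even with the stated 92% taken at face value for stage 2, the proportional effect gives 84.4%.

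The calculations use two-proportion normal approximations, 1:1 allocation, a futility rule that is followed, and no clustering.

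**What to change.** In the protocol and analysis plan, before any interim look:

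1. State the 6-month Bactek rate assumed, with the reason for it, and say explicitly that 182 is a total.
2. Restate stage 2 power as about 90%, and restate stage 1 and overall power for the chosen rate: about 90% and 83% under a proportional effect; about 98% and at most about 89% if the full 15 points are present by 6 months.
3. Give the IDMC the false-stop risk of the p>0.43 rule that follows from this.

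This costs some wording and a line for the IDMC, and the published power becomes less favourable. Only 31 infants had been recruited when the article was written, so there is time.

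Raising the futility threshold, for example to about 0.66, is an option for the sponsor to weigh and not a required correction. It would bring stage 1 power back to 97% at 37% v 27% and cannot inflate type I error, because the look is for futility only. In return, the chance of stopping under no effect falls from about 57% to about 34%, and the trial would continue with an observed effect slightly favouring placebo.

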### Randomisation

Once eligibility has been confirmed and the parents/guardians have consented, randomisation to the intervention is performed. The randomisation list was prepared by an independent CTR statistician. Participants are being randomised 1:1 using minimisation with a random element (p=0.8). Allocations are minimised by gestational age and anti-RSV prophylaxis—both assumed to have a strong prognostic relationship with the primary outcome. Maternal vaccination against RSV was introduced in the UK during the winter of 2024. Although universal anti-RSV prophylaxis may be introduced in the winter of 2025 to replace existing targeted anti-RSV treatment, we already have incorporated plans to stratify the intervention based on receipt of any anti-RSV prophylaxis. To avoid any issues with inadvertent unblinding or dosing errors, multiple births are being randomised to the same arm. Allocation to Bactek or placebo is double blinded, the allocation is not known to clinicians, the infant’s family or the study team with the exception of the independent CTR statistician. The list was uploaded to a web-based randomisation system provided by the Centre for Healthcare Randomised Trials (CHaRT) (University of Aberdeen). A member of staff at the recruiting site performs randomisation on the web-based randomisation system which produces the pack ID that the infant is allocated to and a participant ID. The BALLOON IMP is then prescribed by an appropriately qualified individual. If necessary, unblinding can be performed on the web-based randomisation system by the PI.

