## Discussion

Infants born preterm at ≤29+6 weeks’ gestation are at risk of lung disease in the early neonatal period and subsequently vulnerable to LRTIs during infancy and childhood. These LRTIs may lead to increased healthcare utilisation with visits to GPs, A&E and hospital admissions with time missed from work for the parents. In addition, the LRTIs may exacerbate the existing lung disease. Therefore, it is important to aim to prevent viral infections in infancy. Currently, preventative strategies are largely limited to anti-RSV antibody prophylaxis, maternal RSV immunisation during pregnancy and avoidance of viral infections especially in nurseries. TIBVs, such as Bactek, are increasingly used and provide a promising therapeutic avenue for preterm-born infants to target postdischarge respiratory viral infection in this vulnerable group of preterm-born infants.

We opted to study the preterm-born group below 30 weeks’ gestation at birth as this is the group at the highest risk of developing the important lung disease BPD in the neonatal period, which can have lifelong consequences and thus is an important group for intervention to prevent LRTIs after discharge from the neonatal unit. If this treatment is successful in decreasing LRTIs during the first year of life, there should be large cost savings for the health services throughout the world. The cost to the health service for each hospital admission for a chest infection is over £6000 (in 2012).^22^ Importantly, it will also benefit the parents and their infants. The definition of an LRTI may, in some cases, be difficult to discriminate from an upper RTI. However, any potential LRTI will be verified by research staff at the sites, so this should ensure that the primary outcome is accurate. We have also included the effects of LRTIs on the parents, including time off nurseries and off work. The results should be easily interpretable as we are adequately powered to meet the objectives of the study and will ensure adequate data are collected.

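### The stated stage 2 power of 92% does not match 460 analysable infants, which give about 90%; the stated 90% overall power relies on the 92%

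*Protocol article*

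**What the plan says.** The Sample size section sets the final comparison. On the placebo arm, "we estimated that 55% of participants in the placebo arm would experience a health professional diagnosed LRTI". The target is a 15-point absolute reduction, to 40%, with 15% loss to follow-up. The Randomisation section gives 1:1 allocation.

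The same section describes two stages:

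- **Overall:** "To maintain overall power of 90% and a pairwise one-sided alpha of 0.025, we require 346 recruited participants", of whom 182 have analysable intermediate (6-month) outcome data.
- **Stage 1:** one-sided alpha 0.43 and power 97%. The section puts 37 of the 55 percentage points of LRTI diagnoses in the first 6 months. It gives no active-arm rate at 6 months.
- **Stage 2:** "we would require 542 total recruited participants of whom 460 have analysable definitive outcome data", followed by "The stage 2 one-sided alpha is 0.025 and power is 92" per cent.

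The Interim analysis section treats a one-sided p value above 0.43 as a statistical indication of lack of benefit. It adds that the IDMC may consider other data when it decides whether to stop.

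**The concern.** A two-stage design with a futility look loses some power at the look. To keep 90% overall, stage 2 must have more than 90% by itself, and the stated 92% appears to serve that purpose. But 460 analysable infants looks like the size of an ordinary single-stage trial with 90% power. If so, nothing was added for the futility stage, and the stage 2 power and the overall power are both overstated. Funders, the IDMC and later readers of a null result rely on these figures.

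**Working it through.** **Inputs (Sample size and Randomisation sections).** p1 = 0.55, p2 = 0.40, difference 0.15, one-sided alpha 0.025 (z = 1.960), 460/2 = 230 per arm. Loss to follow-up: 542 × 0.85 = 460.7, which agrees with 460.

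**Step 1. Stage 2 power at 230 per arm.** Power = Φ[(0.15 − 1.960 × SE0)/SE1].

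SE1 = √[(0.55×0.45 + 0.40×0.60)/230] = √(0.4875/230) = 0.04604. SE0 depends on the null variance chosen:

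| Null variance | SE0 | Argument of Φ | Power |
|---|---|---|---|
| Unpooled, 0.4875 | 0.04604 | 1.298 | 90.3% |
| Control rate, 2×0.55×0.45 = 0.495 | 0.04639 | 1.283 | 90.0% |
| Pooled, 2×0.475×0.525 = 0.49875 | 0.04657 | 1.276 | 89.9% |

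Other methods: exact power of the chi-square test 90.0%, arcsine 89.9%, log odds ratio 89.4%, log risk ratio 88.7%. The most favourable variant tried, with the null variance at 40%, gives 90.5%. None gives 92%.

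**Step 2. Work back from the power to the size.** n per arm = [1.960 × √V0 + z(power) × √0.4875]² / 0.15², where V0 is the null variance from the table, z(0.90) = 1.282 and z(0.92) = 1.405.

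| Null variance | n per arm, 90% | n per arm, 92% | Total analysable, 92% |
|---|---|---|---|
| Unpooled | 227.7 | 245.3 | 491 |
| Control rate | 229.8 | 247.5 | 496 |
| Pooled | 230.8 | 248.6 | 498 |

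The control-rate version at 90% gives 230 per arm, so 460 analysable, and 229.8/0.85 rounds up to 271 per arm, so 542 recruited. Both stated sizes are therefore reproduced exactly at 90%. At 92% the need is 491–498 analysable, about 578–586 recruited. The shortfall is 31–38 analysable infants.

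**Step 3. Overall power.** With the rule followed, success means passing stage 1 and then winning at stage 2. Overall power therefore cannot exceed stage 2 power.

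Take the stated 97% and 92% first. A bivariate normal calculation with a correlation of 0.4 to 0.43 between the two test statistics gives 89.9–90.0%, which reproduces the stated 90% overall. With stage 2 power at 90.1% instead, the same calculation gives 88.1–88.2%.

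The correlation comes from √(m/230) × Σq(1−p) / √[Σq(1−q) × Σp(1−p)]. Here m is the interim number per arm, q the 6-month rate and p the 12-month rate in each arm, and sums run over arms.

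**Step 4. Dependence on the unstated 6-month rate.** Assume first that the full 15-point reduction is already present at 6 months (37% versus 22%). The control-rate formula at alpha 0.43 and power 97% then gives 77.1 per arm. Dividing by 0.85 gives 91 per arm, or 182 in total, so 22% may be what the planners used. That is an inference. The proportional alternative is 0.37 × 0.40/0.55 = 0.269.

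| 6-month rates | Interim per arm | Stage 1 power | Overall, 230 per arm | Overall, 248 per arm |
|---|---|---|---|---|
| 37% vs 22% | 77 | 97% | 88.0% | 90.2% |
| 37% vs 22% | 91 | 98% | 88.7% | 90.8% |
| 37% vs 26.9% | 91 | 90% | about 83% | about 85% |

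The first two rows are simulated overall powers (1,000,000 runs). The bivariate normal gives 88.0–88.3% and 88.7–89.1% for 230 per arm. The last row is bivariate normal; simulation gives 82% for 230 per arm.

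**The case against.** **The gap is small.** Stage 2 power is off by 1.7 to 2.1 points, and error control, analysis model and recruitment target are untouched. This stands, and it limits the severity. In sample size, however, the mismatch is 7–8% under every variance choice, and 460/542 reproduces exactly at 90%, so rounding does not explain it.

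**The 92% may be conditional on passing stage 1.** With 37% versus 22% at 6 months, that conditional power is about 90.7%, still not 92%.

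**The futility rule may not bind.** The Interim analysis section lets the IDMC weigh other data. This also stands. A reader might infer that overall power is capped at 89%, or that 90% is impossible. The document does not support that, because a rule that is not enforced costs no power and overall power stays near 90%. It does not bring stage 2 to 92%.

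**Overall power might be read as simply 83%.** That figure needs an active-arm rate of about 27% at 6 months, which the document does not state. With 22% the overall figure is about 89%. Reading 182 as a per-arm number does not settle the matter either: 2 × 182 = 364 exceeds the 346 recruited by then.

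**The Discussion might seem contradicted.** It says "The results should be easily interpretable as we are adequately powered to meet the objectives of the study". Power of 88–90% for the stated effect is compatible with that sentence, so it needs no correction on this ground.

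**Conclusion.** Wrong as written, of minor-to-moderate weight. The 92% and the 460/542 do not come from the same calculation. On the stated inputs 460 analysable infants give about 90% stage 2 power (89.9–90.3%). This conclusion needs no assumption beyond those inputs.

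The overall figure is conditional. It is about 88–89% if the p>0.43 rule is followed and stage 1 has its stated 97% power, and close to 90% if the rule is non-binding. It is about 83% if the rule is followed, the 6-month effect is proportional and 182 is the interim total. With the rule followed, the range to show is therefore about 83–89%, with the 6-month assumption named. The stated 90% overall is recovered at 97% stage 1 power only with a true 92% at stage 2.

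These figures leave out the clustering of multiples, who are allocated to the same arm, and any gain from covariate adjustment. Neither is among the stated sample size inputs.

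**What to change.** In the Sample size section:

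1. Restate stage 2 power as about 90% for 460 analysable infants.
2. Restate overall power as about 88–89% under the stated stage 1 power with the futility rule followed, and say whether the rule is meant to bind.
3. State the active-arm rate assumed at 6 months, and give overall power under the proportional alternative beside it.
4. Derive the sizes and powers of both stages from one documented calculation, so that the quoted figures belong together.

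The cost is a change of wording and a slightly less favourable stated power. Recruitment need not change. If the sponsor prefers to keep 92%, the analysable number would have to rise to about 491–498 (about 578–586 recruited at 15% loss), but this correction does not require it.
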